### Study Design

The study will be conducted as a randomized noninferiority trial comparing 2 arms: an in-person and an eHealth arm, as shown in Figure 1. Each arm will consist of 2 groups with a target of 15 participants each: 1 early intervention group, 1 wait-list group. An additional feasibility arm will take place if the targeted number of study participants (60) is not reached and will be offered to participants who are interested in participating in the study but are not able to commit to the in-person mode of delivery. It will consist of 2 groups, 1 early eHealth group and 1 wait-list eHealth group.

All participants will receive the mindfulness intervention either in person or via eHealth by the end of the 6-month study period. No participants will be excluded from participation based on financial or technical limitations. Should participants not have access to an Internet connection and a mobile phone, tablet, or computer at home, the research assistant will speak with participants and their parent or guardian to explore alternate available resources (ie, connecting at school, at a local library, through a local health center, at a relative’s or friend’s home).

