### Randomization and Blinding

This study will be a single-blinded study (data analysis only). Participants will be coded using Arabic numerals. A research assistant (CV) will receive all questionnaires and saliva samples. Mindfulness facilitators will be unaware of participant identification numbers. Participants will be assigned to 1 of 4 experimental groups following a computer-generated randomization list (permuted block design, using blocks of 2 or 4). No stratification will be used. The allocation sequence will be generated by a statistician not otherwise involved in the project and passed on to a research assistant after patient identification data has been collected (ensuring that those participating in data analysis are kept blind to the allocation of each participant). Allocation sequence will be password-protected and only accessible to the statistician and research assistant. The research assistant will contact participants by phone to inform them to which group they have been randomized.

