### Intervention

The intervention will consist of the 8-week Mindful Awareness and Resilience Skills for Adolescents (MARS-A) program [23,37], an evidenced-informed in-person MBI adapted specifically for youth with chronic health conditions. This program was developed by coauthors DV and JL at British Columbia Children’s Hospital and the University of British Columbia. MARS-A is based on 3 established evidence-based MBIs for adults and adolescents: mindfulness-based stress reduction (MBSR) [6,38], mindfulness-based stress reduction for teens (MBSR-T) [13], and MBCT [39,40]. The content of the program will be the same for in-person and eHealth groups with only minor adjustments for the eHealth group to allow all participants to remain in view of their Web camera during the sessions. All participants will be offered eight 90-minute weekly evening sessions—this represents an adaptation from adult MBSR and MBCT sessions which are typically 150 minutes in length—led by 2 experienced mindfulness providers with committed daily meditation practices (for this study, coauthor NC with the assistance of coauthor EW), who have been trained in facilitating MARS-A and who will also adapt the program for the online group. Also, while the MARS-A program usually includes a silent half-day retreat, this will not be included in the intervention so as not to disadvantage participants in the eHealth group for whom it might not be feasible to create a silent environment for a longer period of time. Sessions will include short meditation practices, breathing exercises, guided discussion (mindful inquiry), and mindful movements adapted to the context of chronic illness. All participants will also receive a copy of a self-help book for adolescents, *The Mindful Teen: Powerful Skills to Help You Handle Stress One Moment at a Time* [37] (by coauthor DV), to encourage regular practice and maintenance of newly acquired mindfulness skills. Every session will start with a brief review of home practice and will close with a discussion of the home practice for the following week. Participants will receive a weekly reminder email before each session to encourage them to complete home practice exercises and to remind them about the date and time of the next in-person or online mindfulness session. A summarized thematic overview of the MARS-A program can be found in Table 3.

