Participants in the in-person groups will meet at the hospital in a designated teen-friendly room containing chairs and yoga mats. Sessions will take place once a week after school from 5:30 PM to 7:00 PM. Participants will have a 5-minute break at the middle of each session, and a snack will be provided.

Participants in the eHealth groups will be encouraged to find a quiet room with as little outside noise and distraction as possible. They will be required to have access to the Internet, a desktop or laptop computer equipped with a webcam or a tablet or mobile phone with webcam function. Participants and facilitators will be connected using the secure password-protected audio-visual platform Zoom Video Conferencing allowing up to 50 different computer connections. With this interface, participants and instructors can see and hear each other and interact in real time. This interface also allows for audio and video recording of mindfulness sessions and allows hosts to restrict access to meeting members who might not behave appropriately during sessions. All in-person and eHealth mindfulness sessions will be recorded and reviewed by a clinical psychologist with experience and expertise in mindfulness for adolescents (coauthor CMH) to ensure delivery of similar content between groups.

**Table 3 table3:** Thematic overview of the Mindful Awareness and Resilience Skills for Adolescents curriculum.

Week	Theme	Content
1	Stress, Depression and Health—Introduction to Mindfulness for Adolescents	Introduction to mindfulness and group expectations Introduction to stress and depression Group and home practices: breathing practice, sitting meditation, and the body scan
2	Foundations of Mindfulness	Developing a practice Key elements of mindfulness Group and home practices: body scan, mindful eating, sitting meditation
3	Informal Mindfulness Practice and Gratitude	Introduction to informal mindfulness practice Gratitude and pleasant events Group and home practices: mindful movement, 3-minute breathing space, walking meditation
4	Unpleasant Experiences, Physical Sensations, Physical Pain	Discussion: making peace with pain, suffering, and unpleasant physical sensations Group and home practices: mindful stretching, 3-minute breathing space, body scan
5	Seeing Thoughts as Thoughts	Cognitive exercise: thought distortions Discussion: mindfulness of thoughts, rumination Group and home practices: sitting meditation, short breathing practices

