### Power Calculations

Sample size was determined on a realistic estimate based on recruitment rates from previous pilot studies. We estimate that 3 months will suffice to recruit 60 participants. With half the participants in the in-person groups and half the participants in the eHealth groups, the study will have 80% power of confirming noninferiority of the eHealth mode of delivery with a margin of 0.45 points on the MAAS-A scale. This margin reflects the change in MAAS-A scores found in the initial validation study of the MAAS in adolescents using an in-person program [41]. Unfortunately, the convenient sample size of 60 participants used for this study will not allow sufficient power to demonstrate noninferiority of secondary outcomes assessed by standardized questionnaires, based on recent mindfulness studies using these measures in adolescent populations [44,45].

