### Data Analysis

Quantitative and qualitative data analysis will take place as described in Table 2. All quantitative analyses will be conducted using SPSS 24th edition (IBM Corp). Descriptive statistics will be used to identify participant demographics and disease characteristics. Quantitative self-report data will be analyzed using 1-way analyses of variance and analyses of covariance as well as paired *t* tests to assess pre-post MBI changes and to compare outcomes in the in-person versus eHealth arms as well as between the early versus wait-list control groups. A margin of 0.45 will be used as a prespecified noninferiority margin. For the primary outcome (mindfulness skills acquisition), the noninferiority question will be based on a confidence interval of 95% (2-sided) in relation to the noninferiority margin for the different treatment groups.

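### The intervention runs in four interactive groups, but the planned interval and the 80% power make no visible allowance for within-group correlation; if that correlation is above zero, the noninferiority test is too lenient

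*Protocol article*

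**What the plan says.** The delivery structure is fixed in Study Design: "Each arm will consist of 2 groups with a target of 15 participants each", one starting early and one after a wait. Randomization and Blinding makes the individual the unit of allocation: "Participants will be assigned to 1 of 4 experimental groups following a computer-generated randomization list (permuted block design, using blocks of 2 or 4".

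Delivery is collective. The Intervention section describes eight weekly 90-minute sessions in which "Sessions will include short meditation practices, breathing exercises, guided discussion (mindful inquiry), and mindful movements adapted to the context of chronic illness". For the eHealth groups it adds that "participants and instructors can see and hear each other and interact in real time". Sessions are "led by 2 experienced mindfulness providers with committed daily meditation practices", and a single pair is named for this study.

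On the analysis, Data Analysis states: "Quantitative self-report data will be analyzed using 1-way analyses of variance and analyses of covariance", together with paired t tests. The primary noninferiority question is settled by a two-sided 95% confidence interval against a margin of 0.45 MAAS-A points. Power Calculations claims 80% power for that margin "With half the participants in the in-person groups and half the participants in the eHealth groups". Neither section mentions an SD, an ICC, a design effect or a term for group. The early versus wait-list split appears only as a comparison to be made, not as a source of variance.

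**The concern.** This is an individually randomized trial with group-delivered treatment. Before treatment, participants are independent. After eight sessions together, they share a peer group, a discussion history and a calendar period, so their MAAS-A scores may be correlated within group. The named methods compute the standard error as if each arm held 30 independent people.

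In a noninferiority trial, a standard error that is too small makes it easier for the interval to clear the margin, so the error runs in favour of the trial's main claim. With two groups per arm, one unusually good or poor group moves the whole arm mean. Within each arm, group is also fully confounded with timing (one early, one wait-list), so the data can say little about how large the group effect is.

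**Working it through.** **Inputs from the protocol.** 30 per arm; 2 groups of 15 per arm; margin 0.45; two-sided 95% interval (one-sided 2.5%); power 80%; expected attrition 10% to 20% (Attrition and Compliance).

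**Inputs not in the protocol (assumptions).** The SD of the MAAS-A comparison and the ICC.

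**Step 1: the plan's own figure.** Without an SD the 80% cannot be reproduced, only inverted. Assuming independence, a true difference of 0 and no dropout:

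SD = 0.45 / [(1.960 + 0.842) × √(2/30)] = 0.45 / (2.802 × 0.2582) = 0.622.

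A noncentral t calculation gives 0.61. At SD 0.622 the standard error is 0.622 × 0.2582 = 0.161 and the interval half-width is 1.96 × 0.161 = 0.315. The 80% at ICC 0 is therefore built into this SD and is not a confirmation of the plan.

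**Step 2: formulas.**
- Design effect: DE = 1 + (m − 1) × ICC, with m the analysed group size.
- One-sided error of the unadjusted interval: 1 − Φ(1.96/√DE).
- Power with the widened interval: Φ(0.45/SE − 1.96), where SE = 0.622 × √(2·DE/n) and n = 2m per arm.

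**Step 3: 15 per group (no attrition).** Example at ICC 0.05: DE = 1 + 14 × 0.05 = 1.70; √1.70 = 1.304; error = 1 − Φ(1.96/1.304) = 6.6%; SE = 0.161 × 1.304 = 0.209; power = Φ(2.149 − 1.96) = 58%.

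| Assumed ICC | DE | One-sided error, unadjusted | Power, widened interval | Half-width, widened |
|---|---|---|---|---|
| 0 | 1.00 | 2.5% | 80% | 0.315 |
| 0.01 | 1.14 | 3.3% | 75% | 0.336 |
| 0.02 | 1.28 | 4.2% | 70% | 0.356 |
| 0.05 | 1.70 | 6.6% | 58% | 0.410 |
| 0.10 | 2.40 | 10.3% | 44% | 0.488 |

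At ICC 0.10 the half-width exceeds the margin itself. A simulation of four groups of 15 (40,000 trials, t-based interval) gave errors of 2.4%, 3.3%, 6.8% and 10.7% at ICC 0, 0.01, 0.05 and 0.10, in line with the formula.

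**Step 4: 12 per group (20% attrition, 15 × 0.8).** Here n = 24 per arm, and attrition alone lowers power to about 71%.

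| Assumed ICC | DE | One-sided error, unadjusted | Power, widened interval (including attrition) |
|---|---|---|---|
| 0.01 | 1.11 | 3.1% | 66% |
| 0.02 | 1.22 | 3.8% | 62% |
| 0.05 | 1.55 | 5.8% | 52% |
| 0.10 | 2.10 | 8.8% | 41% |

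Smaller groups ease the error inflation slightly, but power falls further.

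**Step 5: can the trial estimate the group effect itself?** Four groups minus two arms leaves 2 degrees of freedom. With a t reference on 2 df and 15 per group, the half-width at ICC 0.01, 0.05 and 0.10 becomes about 0.74, 0.90 and 1.07, and power about 32%, 24% and 19%. A random group effect alone would not give a usable primary analysis.

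**The case against.** The ICC is unknown and the design limits it. Individual randomization means groups differ at the outset only by chance. One facilitator pair is described for the study, and recordings are reviewed so that content stays similar. The outcome is an individual self-report. All of this stands, and it is a reason to include ICCs as low as 0.01. It does not make the correlation zero, because peer-group and cohort effects remain.

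A reader might infer that the interval is certainly too narrow, or that the sponsor's 80% is wrong. The protocol supports neither: the first is conditional on an ICC above zero, and the second cannot be checked without an SD. That the power ignored grouping is inferred from silence, although the sample size is described as resting on recruitment rates.

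A reader might also conclude that the primary decision should be tied to one inflated interval, say at ICC 0.05. Nothing in the protocol supports that value. With 15 per group, such a rule has an error of about 0.5% and power of about 60% if the true ICC is 0, and an error of about 5% if it is 0.10.

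Sensitivity analyses may sit in an analysis plan that is not shown. However, the article itself fixes the tests, the interval rule and the power claim, so the point is not a mere omission. The sponsor presents the study as preparation for a larger multicenter trial and names the small sample as a limitation, which lowers the stakes. It does not mention grouping, and it still speaks of confirming noninferiority and of definitive results.

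**Conclusion.** The point holds in conditional form. The design has four interactive delivery groups, and the stated analysis and power make no visible allowance for them. For any positive ICC, the primary interval is too narrow in the direction that favours noninferiority. Over an illustrative ICC range of 0.01 to 0.10, the nominal 2.5% error becomes roughly 3% to 10%. Power with a matching interval is roughly 75% to 44% without attrition and 66% to 41% with 12 analysed per group. These figures rest on an assumed ICC, a back-solved SD of about 0.62, equal group sizes and a normal reference. The direction is firm if any within-group correlation exists; the size is not. What needs correcting is how firmly the trial may claim noninferiority and how the 80% is described.

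**What to change.** **Data Analysis.** Keep the planned interval, and report the primary interval also with its standard error multiplied by √(1 + (m − 1) × ICC), where m is the mean analysed group size, over a prespecified ICC range such as 0.01 to 0.10. Claim noninferiority firmly only if the conclusion holds across that range. Otherwise describe it as dependent on assuming no group effect. State that a random group effect alone is not reliable with 2 degrees of freedom.

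**Power Calculations.** State that the 80% holds only under independence, give the SD behind it, and show the lower figures over the same ICC range.

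**Cost.** Some wording and one extra calculation; no new data and no change to the design. The downside is a wider interval and a less favourable stated power.

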**Figure 1 figure1:**
[figure not shown]
Experimental design of a randomized longitudinal trial comparing in-person versus eHealth delivery of an 8-week mindfulness-based intervention for adolescents with chronic illness.

**Table 1 table1:** Overview of data collection.

Time point/group	Baseline	Time 0	Week 8	Week 16	6 months
Early groups: experimental arm (distance or eHealth). MBI^a^ begins at time 0.	Background data; Research questionnaires	Salivary cortisol; Participant and facilitator logs (weekly for 8 weeks)	Salivary cortisol; Research questionnaires; Semistructured interviews	Research questionnaires	Research questionnaires
Wait-list control groups: experimental arm (distance or eHealth). MBI begins at week 8.	Background data; Research questionnaires	—	Salivary cortisol; Research questionnaires; Participant and facilitator logs (weekly for 8 weeks)	Salivary cortisol; Research questionnaires; Semistructured interviews	Research questionnaires

^a^MBI: mindfulness-based intervention.

At the end of the recruitment period, once eligibility criteria have been verified, randomization will take place to separate participants in the 4 different groups within the in-person and eHealth arms of the study.

### Randomization and Blinding

This study will be a single-blinded study (data analysis only). Participants will be coded using Arabic numerals. A research assistant (CV) will receive all questionnaires and saliva samples. Mindfulness facilitators will be unaware of participant identification numbers. Participants will be assigned to 1 of 4 experimental groups following a computer-generated randomization list (permuted block design, using blocks of 2 or 4). No stratification will be used. The allocation sequence will be generated by a statistician not otherwise involved in the project and passed on to a research assistant after patient identification data has been collected (ensuring that those participating in data analysis are kept blind to the allocation of each participant). Allocation sequence will be password-protected and only accessible to the statistician and research assistant. The research assistant will contact participants by phone to inform them to which group they have been randomized.

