All interviews will take place through the Zoom electronic audio-visual platform and will be led by a female research assistant, coauthor CV (MD). The research assistant will use an interview guide adapted from a study led by coauthor SAK [33]. She will be encouraged to take field notes during the interviews and will have received individual training in conducting semistructured interviews by coauthors EW (MEd) and SAK (PhD), who both have experience leading semistructured interviews and focus groups with youth. Participants will complete the interview in a private room, at home, with no other nonparticipants or researchers present and will be informed that the research assistant is a medical doctor, has limited experience with mindfulness, and has interest in understanding the effects of mindfulness in adolescents with chronic medical conditions. The research assistant will have met with each participant at baseline either in-person or virtually through the Zoom platform for a recruitment meeting. Recordings will be password-protected and only the research assistant (who will also be transcribing the recordings) will have access to them. Transcriptions will be de-identified using a patient code available only to the research assistant. Transcripts will be returned to participants for comment and correction if there is ambiguity at the time of analysis. Data will be analyzed using a grounded theory model [34] until data saturation is reached. Data for secondary outcomes will be collected for all participants. It is expected that research questionnaires will take 15 to 20 minutes to complete.

Saliva samples for cortisol analysis will be drawn at wake-up, at 12:00 PM, at 5:30 PM, and at 7:00 PM on the first and eighth (last) MBI session to capture fluctuations in cortisol levels throughout the course of the day. Participants will receive a reminder phone call the day before each saliva sampling occurs. This will allow for the comparison of pre-post cortisol level differences between participants in the in-person and eHealth arms. Participants in the eHealth arm will be provided with prepaid postage for return of saliva samples, which they will be able to send from home. It has been shown that saliva samples can be exposed to room or exterior temperatures for at least 72 hours without affecting cortisol values [35]. Once received, saliva samples will be kept frozen until they are sent to a specialized laboratory for analysis by enzyme immunoassay [36].

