Transcribed interviews will be analyzed using inductive content analysis [46]. Inductive qualitative content analysis allows for a systematic classification of the data to identify categories based on patterns. By not imposing a preexisting coding schema, inductive content analysis allows for novel insights and understanding from the perspectives of participants grounded in their experiences of attending the MBI either in-person or via eHealth. Coding will be completed in a phased approach using NVivo software (QSR International Pty Lmd). In phase 1, 3 investigators (NC, EW, CV) will review 2 transcripts independently using an inductive open coding approach and then meet to develop codes based on group consensus. Codes will be discussed such that the 3 investigators agree upon (1) the major and minor themes that codes represented and (2) codes could be assigned to meaning units (phrases to several sentences). In phase 2, the same 3 investigators will code an additional 2 transcripts independently using the developed codes and meet again to discuss and confirm the coding structure. In phase 3, 2 investigators (NC, EW) will independently code the remaining transcripts. Investigators will be in contact to discuss findings should any new codes emerge from the data. Should any new codes arise, all previously coded transcripts will be reviewed for new codes. If there are disagreements among the 2 investigators, the third investigator will code to arrive at a consensus and ensure consistency with original coding structure. In phase 4, the 3 investigators will meet to collapse all resulting codes into categories. Given the ongoing communication and coding to consensus, interrater reliability will not be calculated. Major and minor themes will be presented using participant quotes (identified by participant number) in the final account of study results.

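### The article says, without exception, that data analysts are blind to allocation; this cannot hold for the interview coding, done by the two session facilitators and the research assistant

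*Protocol article*

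**What the plan says.** Under Randomization and Blinding the article states: "This study will be a single-blinded study (data analysis only"). The sequence is generated by an outside statistician and passed to a research assistant, a procedure described as "ensuring that those participating in data analysis are kept blind to the allocation of each participant". On access it says: "Allocation sequence will be password-protected and only accessible to the statistician and research assistant". On disclosure to participants: "The research assistant will contact participants by phone to inform them to which group they have been randomized".

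Two partial safeguards are given. The same section says: "Mindfulness facilitators will be unaware of participant identification numbers". Data Collection adds that transcripts are de-identified with a code that only the research assistant holds. That person also conducts every interview and transcribes the recordings.

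The Intervention section says the sessions are "led by 2 experienced mindfulness providers with committed daily meditation practices", and identifies both providers by initials. The Data Analysis section names three interview coders, also by initials: the same two providers and the research assistant. All three code the first transcripts and settle the coding structure. The two providers then "will independently code the remaining transcripts", with the third coder brought in where they disagree.

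**The concern.** The blinding statement covers data analysis as a whole. The Data Analysis section opens by addressing quantitative and qualitative analysis together, and the interview coding is described within it. On the article's own terms, the coders take part in data analysis and should be blind. Their other duties in the trial make that impossible.

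What is at stake is how the acceptability results will be read. Participant appreciation is a listed secondary outcome. The hypothesis includes high acceptability in both arms, and the Discussion anticipates excellent acceptability in person and similar results by eHealth. Participants' comments on the programme will be coded by the people who delivered it and the person who interviewed them. No interrater reliability will be calculated, and Strengths and Limitations does not mention the arrangement. A reader who relies on the blinding section would take this analysis to be masked.

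**Working it through.** No arithmetic is needed beyond a count. The check sets who learns the allocation against who analyses the interviews.

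| Interview coder | Other trial role (section) | How allocation becomes known | Part in coding (Data Analysis) |
|---|---|---|---|
| First facilitator | Leads sessions in both arms (Intervention) | Meets each participant in the assigned group | Phases 1 to 4 |
| Second facilitator | Assists in leading the same sessions (Intervention) | Same | Phases 1 to 4 |
| Research assistant | Holds the list and informs participants (Randomization and Blinding); interviews, transcribes, holds the patient code (Data Collection) | Directly from the list, and again in the interview | Phases 1, 2 and 4; in phase 3 only where the other two disagree |

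1. **Count.** 3 of 3 named coders learn allocation through their role. No coder without such a role is named in any of the four phases.

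2. **Volume.** Phases 1 and 2 use 2 + 2 = 4 transcripts, coded by all three. With a recruitment target of 60, at most 60 − 4 = 56 remain for phase 3. This is a ceiling: attrition would lower it, and the interview data are to be analysed until saturation.

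3. **Do the safeguards restore blinding for the facilitators?** In part. They code de-identified text, were not present at the interviews and have no access to the recordings or the key. They may therefore not know whose transcript they are reading. The arm is harder to hide, because the stated purpose of the coding is to understand how participants experienced the programme in person or by eHealth. A transcript on that subject will usually reveal the delivery mode. This is an inference from the subject of the interviews; the article does not state it.

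4. **Do they restore it for the research assistant?** No. This person holds the key, conducted the interviews and typed the transcripts.

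5. **Is it one research assistant?** The sentences on the allocation list carry no initials. Only one research assistant is described, and is identified by initials earlier in the same section, so the identification is an inference, though a strong one. If a different assistant held the list, the interviewer would still learn each participant's delivery mode in the interview.

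**The case against.** The strongest reply is that the blinding statement was meant for the quantitative data. The sentences around it concern numeric participant codes, questionnaires and saliva samples. Unblinded coding is not improper in qualitative work, and the coders' roles are openly given by initials. All of that is fair, and it shows that nothing is concealed. It does not rescue the statement, which contains no such limit; a reader must match initials across three sections to discover one.

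Several stronger readings are tempting, and the article does not support them.

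- A reader might infer that the facilitators know whose transcript they are coding. De-identification, with the key held elsewhere, speaks against assuming this.
- A reader might infer that the facilitators have sole charge of phase 3. The third coder resolves disagreements, and all three form the final categories.
- A reader might see a contradiction between facilitators not knowing identification numbers and the plan to label published quotations by participant number. There is none: a number can be visible on a transcript without the key that links it to a person.
- A reader might extend the point to the outcome on adapting the programme for eHealth. Table 2 draws that from facilitator log books, which are the facilitators' own impressions by design, and not from the coded interviews.

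The absence of interrater reliability is explained in the article by coding to consensus, and is not by itself a fault.

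**Conclusion.** The point stands in a narrow form. The article claims, without exception, a blinding that its interview analysis does not have: 3 of 3 coders acquire allocation knowledge through their trial roles. For the research assistant the lack of blinding is certain from the interviewing and transcribing alone. For the facilitators it is probable as to arm and not established as to individual, on the assumption that transcripts reveal the delivery mode.

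The effect is confined to participant appreciation and the acceptability conclusion drawn from it. A reader might go on to infer that blinding also fails for the primary noninferiority comparison. The article does not say who carries out the quantitative analysis, so there is no basis for that, whether for the MAAS-A, the other questionnaires or cortisol. The direction and size of any bias in the coding cannot be determined from the article.

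**What to change.** - **Randomization and Blinding:** limit the statement to the quantitative analysis, and say that interview coding is not blinded. The limited statement should be made only if the quantitative analyst has no access to the allocation list; the article does not establish this, so it must be confirmed first.
- **Data Analysis:** state that the interview coders are the two session facilitators and the research assistant who holds the allocation list and patient code.
- **Strengths and Limitations:** list this as a limitation on the acceptability findings, noting that de-identification may conceal the participant from the facilitators but probably not the arm.

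The sentence about facilitators not knowing identification numbers can stay as it is. The point does not require a change of coders. The cost is a few sentences and a less favourable blinding statement; the sample, the data collection and the quantitative analysis are unaffected.
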